## Abstract

**Background:**

Peritoneal dialysis (PD) remains underutilised in Germany, prompting the initiation of the Sustainable Intensification of Peritoneal Dialysis in Schleswig–Holstein (SKIP-SH) project. The SKIP-SH cohort study aims to demonstrate the presumed benefits of PD, including enhanced quality of life and reduced healthcare personnel requirements, and to generate data to strengthen the use of PD.

**Methods:**

The prospective SKIP-SH cohort study recruits patients with advanced chronic kidney disease (CKD) and their caregivers. Comprehensive data, including demographic information, medical history, clinical course, laboratory data, and quality-of-life assessments, are collected. Additionally, biomaterials will be obtained.

Primary study objectives are documenting the clinical course and complications, time on therapy for new dialysis patients, reasons influencing treatment modality choices, circumstances at the initiation of dialysis, and quality of life for patients with CKD and their caregivers. The collected biomaterials will serve as a basis for further translational research. Secondary objectives include identifying factors impacting disease-related quality of life, clinical complications, and therapy dropout, estimating ecological footprints, and evaluating healthcare costs and labour time for initiating and sustaining PD treatment.

**Discussion:**

PD is notably underutilised in Germany. The current therapy approach for advanced CKD often lacks emphasis on patient-focused care and quality-of-life considerations. Furthermore, adequate explorative research programs to improve our knowledge of mechanisms leading to disease progression and therapy failure in PD patients are scarce.

The overarching goal of the SKIP-SH cohort study is to address the notably low PD prevalence in Germany whilst advocating for a shift towards patient-focused care, quality-of-life considerations, and robust translational research.

**Trial registration:**

This study was registered with the German trial registry (Deutsches Register klinischer Studien) on November 7, 2023, under trial number DRKS00032983.

## Background

People with advanced chronic kidney disease (CKD) require kidney replacement therapy (KRT) when the vital functions of the diseased kidneys fail. The most common form of KRT, haemodialysis (HD), is typically delivered in specialised facilities (dialysis centres). However, a proportion of affected patients could potentially undergo peritoneal dialysis (PD), which many can perform independently at home and usually need to visit the dialysis centre only monthly or less.

The two dialysis methods are considered equivalent as patients using them have similar life expectancies [1, 2]. However, PD is advantageous for many people from the quality-of-life perspective because independent therapy implementation allows for greater freedom in everyday life [3, 4]. Another advantage of PD is that the procedure is potentially more cost-effective and efficient than HD because less support is required from healthcare professionals, and the costly transportation to and from the dialysis centre can be minimised [5–7].

Due to historically evolved structures, PD is hardly used in Germany, and well over 90% of patients requiring chronic dialysis perform HD. This situation is particularly pronounced in the northernmost German federal state of Schleswig–Holstein. Here, only 4.3% of dialysis patients perform PD, which appears to be severely underused [8, 9]. Due to its many remote regions and islands with low population density, Schleswig–Holstein is highly suitable for using PD to increase the proportion of people treated at home. Expanding PD use would also reduce the number of in-centre HD patients and ease the workload on the already scarce and burdened specialist staff in HD centres. Intensifying PD use in Schleswig–Holstein could improve the quality of life of respective patients and save considerable costs and resources without limiting the quality of patient care and life expectancy.

Unfortunately, PD cannot be performed indefinitely. During the course of PD therapy, patients develop increasing peritoneal fibrosis and inflammation [10, 11]. These processes lead to detrimental changes in peritoneal transport properties and ultimately to technical failure of the procedure, typically after approximately five years, although prospective studies on this matter are scarce [12, 13]. In the worst case, a potentially fatal condition known as “encapsulating peritoneal sclerosis” develops [14, 15]. The condition shows great variability in between different countries, but in recent years there has been a decline in the incidence. This decline has been attributed to newly developed PD solutions and treatment strategies [16, 17]. Demonstrating the capability to influence one of the most feared complications of PD shows the immense potential and need for future translational research in this area.

Currently, high structural barriers restrict the further spread of PD. There is a lack of established treatment pathways and the necessary technical expertise due to the low prevalence of PD in many places. To address this problem, we launched *The Intersectoral Coordination Unit for the Sustainable Intensification of Peritoneal Dialysis in Schleswig–Holstein* (SKIP-SH) project at our clinic (Fig. 1). SKIP-SH constitutes a comprehensive initiative designed to augment the prevalence of PD among patients in the region. At its core, this project entails the establishment of a pre-dialysis coordination office to optimise shared decision-making with patients towards the most appropriate dialysis modality and mitigate existing institutional barriers that impede PD adoption. Additionally, SKIP-SH aims to create a training and education structure for patients and medical staff, creating a robust framework for sustainable PD implementation in Schleswig–Holstein. The SKIP-SH cohort study presented here aims to follow the SKIP-SH project and provide data-based proof for the assumed benefits of increased PD use.

**Fig. 1 Fig1:**
[figure not shown]
Schematic representation of the Peritoneal Dialysis Coordination Unit functions as an interface between patients and outpatient and inpatient care facilities (CKD = chronic kidney disease, PD = peritoneal dialysis, KRT = kidney replacement therapy, SKIP-SH = Intersectoral Coordination Unit for the Sustainable Intensification of Peritoneal Dialysis in Schleswig–Holstein)

## Methods/Design

### Study aims and design

The SKIP-SH cohort study was designed as an accompanying prospective registry study to the clinical SKIP-SH project, which aims to sustainably strengthen PD use in Schleswig–Holstein.

This study aims to determine whether the theoretical benefits of PD are evident in practice and encourage translational research on PD. To do so, we have defined primary and secondary objectives as listed in Table 1.

**Table 1 Tab1:** Study objectives

Primary objectives	Secondary objectives
Documentation of clinical course, complications, and time on therapy of new dialysis patients	Identification of factors influencing good or poor disease-related quality of life of PD patients
Documentation of the reasons for choosing the treatment modality and the circumstances at the start of dialysis	Identification of factors influencing occurrence of clinical complications and dropout from therapy in PD patients
Documentation of quality of life of patients with CKD starting dialysis and their caregivers before, during, and after dialysis treatment initiation	Estimation of the ‘ecological footprint’ of PD patients
Establishment of a biomaterial bank of patients with CKD starting dialysis	Estimation of health care costs and labour time required to start and maintain PD therapy

### Participant characteristics and inclusion and exclusion criteria

All patients presenting at our pre-dialysis coordination office with CKD stage 4 or 5 (estimated glomerular filtration rate < 30 mL/min/1.73 m^2^ for at least three months)[18] and their family caregiver (living in the same household) are eligible for inclusion in the study. Family caregivers will only undergo the quality-of-life assessment part of the study. All the inclusion and exclusion criteria are summarised in Table 2.

**Table 2 Tab2:** Inclusion and exclusion criteria

Inclusion criteria	Exclusion criterion
Patients with CKD stage 4 or 5	Inability to give informed consent
Family caregiver of a patient with advanced CKD	
Age ≥ 18 years	

Recruitment started on 1 December 2023 and is scheduled to run for three years; the follow-up will continue at least until 30 November 2028.

In line with the trend of patient numbers that we provided with a permanent dialysis access at our centre annually in recent years, we estimate that ~ 100 eligible patients with CKD qualifying for potential inclusion in the study will present to our pre-dialysis coordination office every year. We expect that the majority of these patients will start a dialysis procedure during the observation period. Patients will be followed up regardless of the dialysis modality they will eventually choose (PD or HD). We expect to include half as many family caregivers as patients.

### Processes, interventions, and comparisons

#### Procedure for informing and obtaining consent

Study information will be provided and written informed consent for participation will be obtained during a meeting between one of the investigators and eligible patients and/or their caregivers at our pre-dialysis coordination office.

#### Data sources

All relevant clinical information and biomaterials will be obtained from the study participants, medical records in our clinic, and the treating physicians in outpatient offices. Quality of life data will be assessed with questionnaires (delivered either in person, by mail, or in a digital form) at predefined time points (applies to patients and caregivers).

#### Data and materials to be collected

The collected dataset will include demographic parameters, clinical trajectory data, laboratory values, biomaterials, quality-of-life assessments, housing conditions, and essential working hours for medical personnel (Table 3).

**Table 3 Tab3:** Specific data to be collected

**Category**	**Detailed data**
Demographic data	Age; sex; marital status; ethnicity; weight; height; housing details (number of persons in the household, living space in square meters, rent/ownership); care level (if applicable)
Medical history	Comorbidities; current medication use; circumstances of and preparation for starting of dialysis; current dialysis regimen (including number of weekly sessions, Kt/V, dialysate composition and volume, incremental dialysis regimens, if applicable); residual urine excretion (if applicable); reasons for choice of dialysis type (personal preference/medical indications)
Clinical course	Number, duration, and reason for hospital admissions since start of dialysis/in the last year/since the last visit; frequency of outpatient medical consultations and laboratory checks; complications associated with the dialysis procedure; cardiovascular complications; need for care/increase of care level; date and cause of death (if applicable)
Estimated working time of medical staff in association with dialysis treatment	Duration of medical and nursing consultations; time required for learning the dialysis procedure
Laboratory data (as available from routine healthcare)	Blood count; electrolytes; clinical chemistry; lipid status; urinalysis
Quality of life	‘Kidney Disease Quality of Life 36-Item Short Form Survey (KDQOL-36)’ for patients and ‘Burden Scale for Family Caregivers (BSFC)’ for family caregivers
Biomaterials	Whole blood (15 mL per timepoint) and overnight peritoneal effluent

Only basic demographic data and quality of life will be collected from family caregivers; the remaining items will be collected only from the patients.

Table 4 delineates the designated time points for study visits and data/biomaterial collection. Study visits that do not require sampling of biomaterials may be completed via remote communication.

**Table 4 Tab4:** Data acquisition time points

Time point	First presentation (V0)	Start of dialysis/change of dialysis modality^a^ (V1)	+ 3 months^a, b^ (V1.2)	+ 6 months^a, b^ (V1.3)	+ 12 months (V2)	Annually thereafter (V3, V4, V5, etc.)
Demographic data	x					
Medical history	x	x	x	x	x	x
Clinical course	x	x	x	x	x	x
Estimated working time		x	x	x	x	x
Laboratory data	x	x	x	x	x	x
Quality of life	x	x	x	x	x	x
Biomaterials	x	x			x	x

^a^If the first presentation takes place after the start of dialysis and no change in dialysis type occurs, visits V1-V1.3 will be skipped

^b^May be completed via remote communication

The biomaterials obtained will include blood samples and overnight PD effluent. Samples will be stored to allow for analyses of the transcriptome, DNA(-methylation)-profiling, immunophenotyping of blood leukocytes and cells in the PD effluent, as well as analyses of serum and plasma markers, and soluble markers in the PD effluent.

Digital data documentation and biomaterial storage will be pseudonymised; only the study investigators will have access to the information that enables re-identification.

While data and biomaterials will be stored indefinitely, study participants can revoke their consent at any time and may request the deletion of their data and disposal of their biomaterials.

The publication and provision of data or biomaterials to third parties for scientific purposes will be done exclusively in an anonymised manner.

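### Table 4 footnote a sets no time limit, so recent dialysis starters who do not change dialysis type lose 3- and 6-month visits that are still ahead

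*Protocol article*

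**What the plan says.** Table 4 (Data and materials to be collected) schedules a first presentation (V0), a visit at start of dialysis or change of modality (V1), visits 3 and 6 months on (V1.2, V1.3), a 12-month visit (V2) and annual visits after that. Footnote a is attached to V1, V1.2 and V1.3: "If the first presentation takes place after the start of dialysis and no change in dialysis type occurs, visits V1-V1.3 will be skipped". Footnote b allows V1.2 and V1.3 to be done remotely, and neither visit has biomaterials marked.

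Patients already on dialysis are in scope. Eligibility covers "All patients presenting at our pre-dialysis coordination office with CKD stage 4 or 5", and the only exclusion in Table 2 is being unable to consent. Footnote a itself provides for such patients.

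Three primary objectives in Table 1 concern the period around dialysis start:
- "Documentation of quality of life of patients with CKD starting dialysis and their caregivers before, during, and after dialysis treatment initiation"
- "Documentation of clinical course, complications, and time on therapy of new dialysis patients"
- "Documentation of the reasons for choosing the treatment modality and the circumstances at the start of dialysis"

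Quality of life is measured by questionnaire at set time points in patients and caregivers. At V0, Table 4 marks demographics, medical history, clinical course, laboratory data, quality of life and biomaterials. It does not mark estimated working time, which begins at V1.

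**The concern.** The rule suits someone years into dialysis: the early visits are long past and cannot be held. It is applied equally to someone days or weeks in, for whom the 3- and 6-month visits could still take place. That person is a new dialysis patient in the sense of the primary objectives.

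A quality-of-life score not taken at 3 or 6 months cannot be rebuilt from records. Whether a patient contributes one depends on how that patient reached the coordination office, so the 3- and 6-month data describe a selected group. The Statistical analysis section singles out PD against HD as the group comparison of most interest. Any such comparison at 3 or 6 months would inherit this selection.

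**Working it through.** The document gives no figure on this point, so there is none to reproduce. The check sets the footnote against the schedule, then illustrates size on stated assumptions.

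**Step 1: which visits are still possible.** Let t be months from actual dialysis start to first presentation, with no change of dialysis type.

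| t | V1 | V1.2 | V1.3 | Held under footnote a |
|---|---|---|---|---|
| under 3 | passed | ahead | ahead | none |
| 3 to under 6 | passed | passed | ahead | none |
| 6 or more | passed | passed | passed | none |

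Only in the last row does the skip merely record what is already past. V1 has always passed; only V1.2 and V1.3 can be lost needlessly.

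Example: at t = 0.5, quality of life is measured at V0 and next at V2. The article does not say what V2 counts from when V1 is skipped. Counted from dialysis start, the gap is 12 − 0.5 = 11.5 months; counted from V0, it is 12 months and V2 falls at month 12.5.

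**Step 2: what is lost and what is kept.**

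| Item | Position under footnote a |
|---|---|
| Quality of life at 3 and 6 months (patient and caregiver) | lost; one score at V0, next at V2 |
| Laboratory and clinical-course entries dated at 3 and 6 months | lost as scheduled entries |
| Working time | nothing before V2 |
| "circumstances of and preparation for starting of dialysis", and reasons for modality | kept, under medical history at V0 |
| "Number, duration, and reason for hospital admissions since start of dialysis/in the last year/since the last visit" | kept, under clinical course at V0 and V2 |
| Dialysis-related and cardiovascular complications, death | kept, under clinical course at V0, V2 and later |

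**Step 3: illustration of size.** From the document: about 100 eligible patients a year for three years of recruitment, so N = 100 × 3 = 300. This counts patients who could be included, not those enrolled, and some may never start dialysis. Assumed, because the document gives none of them:
- s, the share first seen after dialysis start with no change of type: 5% to 40%
- r, the share of those seen before month 6: 25% to 100%
- d, the difference in quality of life between omitted and included patients: 0.3 to 0.5 SD, in either direction

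Patients without V1 to V1.3 number N × s: 300 × 0.05 = 15 to 300 × 0.40 = 120. Those who would regain V1.3 if only past visits were skipped number N × s × r. Their share of the 6-month group so completed is w = sr / (1 − s + sr), and the shift in the 6-month mean caused by the footnote is w × d.

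| s | r | Regained | w | Shift (SD) |
|---|---|---|---|---|
| 5% | 25% | 3.75 | 3.75/288.75 = 1.3% | 0.004 to 0.006 |
| 5% | 100% | 15 | 15/300 = 5% | 0.015 to 0.025 |
| 40% | 25% | 30 | 30/210 = 14.3% | 0.043 to 0.071 |
| 40% | 100% | 120 | 120/300 = 40% | 0.12 to 0.20 |

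At 3 months, r is the share seen before month 3, which cannot be larger, so for the same s and d the shift is no larger. Within one modality, s is the share in that modality. A PD-HD contrast moves only so far as the two groups differ in w or d.

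**The case against.** The best defence is that little is lost. This is an observational registry with exploratory analyses, group comparisons are planned only as far as feasible, and no 3- or 6-month PD-HD contrast is specified. V0 takes nearly everything V1 would, and clinic records and treating physicians are further sources. Clinical course, complications and time on therapy can therefore still be documented, provided the analysis allows for entry after dialysis start. Patients who change dialysis type are exempt from the skip. The labour-time objective is secondary and worded for PD only, so missing working time in a patient who stays on HD falls outside it. All of this stands, and it narrows the loss to the items shown as lost above. It does not restore the 3- and 6-month questionnaires, which serve a primary objective and have no other source.

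A reader might go further and infer that early-dialysis results leave these patients out altogether. They do not, given what V0 and V2 collect. A reader might also infer that those omitted are mostly unplanned starters, sicker and on HD, so that early HD results look too favourable. That is a plausible guess about people who reach a pre-dialysis office after starting. However, the document does not say how many such patients are expected, how recently they started, whether the start was planned, or which modality they use.

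**Conclusion.** The point holds in a limited form. As written, footnote a discards obtainable 3- and 6-month visits for recent starters who stay on the same dialysis type. Results at those times then rest only on patients seen before dialysis start or who switch modality. That follows from the text alone.

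The size does not. On the assumed ranges, the 6-month mean could shift by anything from under 0.01 SD to 0.20 SD. The top value needs 40% of patients to be late presenters, all of them seen before month 6, and a 0.5 SD difference. The direction of any bias is not derivable, and no claim that HD or PD would be favoured is supported. This is a cheap improvement to a data-collection rule, not a flaw that undermines the study.

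**What to change.** Amend footnote a so that only visits whose due date, counted from the actual start of dialysis, has passed at first presentation are skipped. The remaining V1.2 and/or V1.3 are held, remotely if needed, with the caregiver questionnaire on the same dates.

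For patients first seen within 6 months of dialysis start:
- collect the working-time items at V0;
- record V0 with its actual time since dialysis start and do not file it as a start-of-dialysis value, since a month-5 score labelled as a start value would mix timings in the primary quality-of-life objective;
- count the 12 months to V2 from dialysis start.

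Patients 6 months or more into dialysis are still spared all three visits. The cost is a short change to one footnote, the working-time items at V0, and at most two extra visits per affected patient (two if first seen before month 3, one if between months 3 and 6). Those visits may be remote and need no biomaterials.

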### Statistical analysis

An overview of the collected data and the study participants will be summarised annually in interim reports during the study period. Exploratory statistical analyses of the study objectives will be conducted as appropriate. This includes an analysis of the correlation between specific characteristics and dialysis regimes on the clinical course and outcomes. As far as feasible, group comparisons will be made between patients on different dialysis regimes, in particular the comparison between PD and HD patients.

Demographic factors and patient characteristics will be compared using the Mann–Whitney *U*-test, Student’s *t*-test, or the Chi-squared test as appropriate. Descriptive analysis will include frequency distribution, medians and interquartile ranges (IQRs), and/or means and 95% confidence intervals. Multivariable regression models will analyse the effects of various variables on outcomes of interest. Time-to-event analyses will be conducted using Kaplan–Meier plots, competing risk analyses, or Cox regression models. Binary variables will be modelled using logistic regression. Statistical significance was set at *p* < 0.05.

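### Student's t-test is named for comparing patient characteristics; if PD and HD groups differ in both size and spread it misses its 5% level, and Welch's test does not

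*Protocol article*

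**What the plan says.** All of the following is in the protocol article.

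- **Tests.** Under Statistical analysis: "Demographic factors and patient characteristics will be compared using the Mann–Whitney" U-test, Student's t-test or the chi-squared test, the choice being left to what is appropriate. No unequal-variance t-test and no small-count alternative to chi-squared is listed. The threshold follows: "Statistical significance was set at" p < 0.05. Sidedness is not stated.
- **Groups.** The paragraph before it says that, where feasible, "group comparisons will be made between patients on different dialysis regimes, in particular the comparison between PD and HD patients". The sentence on characteristics does not itself name the groups or a time point.
- **Status.** "Exploratory statistical analyses of the study objectives will be conducted as appropriate".
- **Other planned output.** The same section plans frequencies, medians with interquartile ranges, means with 95% confidence intervals, and multivariable regression.
- **Size.** Under Participant characteristics and inclusion and exclusion criteria: "we estimate that ~ 100 eligible patients with CKD qualifying for potential inclusion in the study" will present each year, and "Recruitment started on 1 December 2023 and is scheduled to run for three years". No PD share is given for the cohort. The Background reports that in the region "only 4.3% of dialysis patients perform PD", and describes a project meant to raise that figure.

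**The concern.** Student's t pools the two group variances. The pooled value is dominated by the larger group, while the uncertainty of the mean difference comes mostly from the smaller one. When both the sizes and the SDs differ, the standard error is therefore wrong. It is too small if the smaller group is the more variable, and too large if it is the less variable. PD and HD patients arrive at their modality by preference or medical indication, so a difference in spread is plausible for some characteristics, although the article gives no SDs.

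Two things are at stake. First, the Discussion makes the link between living conditions and choice of modality a question of interest, so some of these tests carry inference and their error rate matters. Second, readers often take a table of non-significant p-values as a sign that two groups are alike. With a small PD group that reading would be unsafe, and the PD versus HD outcome comparison would inherit the mistake.

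**Working it through.** The article states no sample size, power, SD or PD:HD ratio, so there is no figure of its own to reproduce.

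**Inputs from the article.** About 100 eligible patients a year for 3 years: 100 × 3 = 300, a ceiling that assumes all enrol and start dialysis. Threshold 0.05.

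**Assumptions.** Two-sided tests, normally distributed data, PD shares of 4.3%, 10%, 20%, 30% and 50% (13/287, 30/270, 60/240, 90/210 and 150/150 PD/HD patients), and PD/HD SD ratios of 0.67, 1.0 and 1.5.

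**1. Why Student's t drifts.** Set the HD SD to 1 and the PD SD to r.

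- True SE of the mean difference: √(r²/n₁ + 1/n₂).
- SE that Student's t uses: s_p·√(1/n₁ + 1/n₂), where s_p² = [(n₁−1)r² + (n₂−1)]/(n₁+n₂−2).

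For 30/270 and r = 1.5:

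- true SE = √(2.25/30 + 1/270) = 0.2805
- s_p² = (29 × 2.25 + 269)/298 = 1.1216
- SE used = √1.1216 × 0.1925 = 0.2038
- ratio = 0.2038/0.2805 = 0.727

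The critical value of 1.968 then acts like 1.968 × 0.727 = 1.43, which gives a two-sided error of about 15%.

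**2. Simulated type I error at nominal 5%** (20,000 runs per setting)

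| PD/HD patients | Student, r = 0.67 | Student, r = 1.0 | Student, r = 1.5 | Welch, all three r |
|---|---|---|---|---|
| 13/287 | 0.4% | 4.9% | 17.5% | 4.8–5.2% |
| 30/270 | 0.8% | 5.0% | 15.3% | 5.0–5.1% |
| 60/240 | 1.3% | 4.9% | 12.2% | 4.9–5.1% |
| 90/210 | 2.2% | 5.0% | 9.2% | 4.9–5.1% |
| 150/150 | 5.2% | 4.9% | 5.3% | 4.9–5.2% |

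Repeat runs move the entries by a few tenths of a percentage point (90/210 also gave 2.3% and 9.4%). Both conditions are needed: with equal SDs there is no distortion even at 13/287, and with equal sizes there is none at either SD ratio.

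**3. What a non-significant result can show.** With equal SDs, the power for a standardised difference d comes from the non-central t distribution with non-centrality d/√(1/n₁ + 1/n₂). For d = 0.3:

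- 13/287: 0.3/0.2836 = 1.06, missed in about 82% of studies
- 30/270: 0.3/0.1925 = 1.56, missed in about 66%
- 60/240: 0.3/0.1443 = 2.08, missed in about 46%
- 150/150: 0.3/0.1155 = 2.60, still missed in about 26%

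**4. Whether a fixed cut-off of 0.1 on the standardised difference would do instead.** For a truly balanced characteristic, the chance that the observed value exceeds 0.1 is 2[1 − Φ(0.1/SE)]. With SE = 0.2836, 0.1925 and 0.1443 this is about 72%, 60% and 49% at 13/287, 30/270 and 60/240. Such a flag would mostly report noise.

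**5. Sparse tables.** With 30 PD patients, a characteristic present in 10% has an expected PD count of 30 × 0.10 = 3, too few for the usual chi-squared approximation.

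**The case against.** The strongest reply is that the article leaves the choice of test to what is appropriate and so fixes Student's t for no variable. Choosing Welch or Fisher case by case is the sort of detail a full analysis plan settles. The work is exploratory and no decision hangs on these tests. Most of this stands, and it is why the point is minor. However, Student's form is the only t-test named, and the article does not say what governs the choice.

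A reader might also infer several stronger criticisms that the article does not support:

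- **That p-values are the only means of judging PD/HD comparability.** The next sentence plans medians with interquartile ranges and means with 95% confidence intervals, so the size of differences will be visible.
- **That the tests will declare the groups balanced or select covariates.** Nothing says so. The regression models are not made conditional on them.
- **That a small or unequal PD group by itself invalidates Student's t.** It does not; the SDs must differ as well, and the article gives none.
- **That the PD group will be about 13 patients.** The 4.3% is a regional figure for all dialysis patients. The cohort comes from an office set up to widen PD use.
- **That testing characteristics is misplaced, as in a randomised trial.** Differences between modality groups are partly a study question here, so dropping the tests would remove inference from a stated aim.

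**Conclusion.** The point holds in a limited form. Student's t is the wrong default for a comparison whose groups are likely to be unequal in size, because an equally simple test is safe whether or not the SDs differ. At assumed PD shares of 4.3% to 30% among 300 patients, the true error is about 9% to 17% at an SD ratio of 1.5 and about 0.4% to 2.3% at 0.67. Welch's test stays near 5%. If the SDs are equal or the groups balanced, there is no distortion.

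Separately, a non-significant difference would be weak evidence that PD and HD patients are alike. The article does not claim otherwise, so this is a caution for reporting rather than an error in the plan.

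The sizes rest on assumed PD shares, SD ratios, normality, two-sided testing and the 300-patient ceiling; fewer patients would lower power further. The consequence is small, since the analyses are exploratory.

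**What to change.** 1. Replace Student's t-test with Welch's t-test wherever a t-test is used, and name Fisher's exact test for sparse tables.
2. Keep the planned summaries and tests, and add standardised differences with confidence intervals by modality, without a fixed 0.1 cut-off.
3. State that a non-significant p-value will not be taken as evidence that PD and HD patients are comparable.

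The cost is a few lines of wording and one extra column of results; no new data are needed. Welch's test gives essentially the same error rate as Student's when the SDs are equal (4.9% for both at 13/287).
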